#### Arm B—conventional treatment only

The patients will use conventional therapy (artificial tears, ciclosporine drops and punctal plugs/cautery) as recommended by their treating ophthalmologist.

### Qualitative approach

A nested qualitative approach using in-depth, semistructured interviews will help us understand the lived experience of people using FAB and factors relating to the ways that clinical departments and healthcare professionals adapt to working with FAB. Topics, questions and probes in the interviews will emerge from three sources: the relevant literature; our experience of and involvement in clinical ophthalmology; and consultation with patients. In this feasibility study, we will use a convenience sampling technique for the qualitative work. We will interview all clinicians who administer the intervention in the study and we will aim to interview 10 patients (adjusted for setting, gender and age group representation). Given the resources, we will aim to draw findings from a larger sample in a future study. This phase will work in parallel to the quantitative data collection so that emerging themes can be investigated in later interviews. Even though the feasibility study sample is reasonably limited, we anticipate some useful insights about the use of FAB because of the triangulation between the RCT and the qualitative findings (for example, reasons for partial adherence).

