Interviews will be recorded, transcribed and analysed using the framework analysis. We will structure the analysis of collected data to fit two evaluation frameworks relevant to the successful implementation of FAB:Patient-oriented: Understand the lived experience of patients using FAB with emphasis on intervention acceptability, perceived enablers and barriers for adherence, perceived clarity of advice, and guidance and factors relating to the initial uptake of the intervention.Organisation-oriented: Whether and how the use of FAB affected workload and/or workflow; identify process change, adaptation challenges, skills gap; establish treatment fidelity and clinician acceptability.

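### The 10 patient interviews are chosen by convenience, so they may include few or no patients who stopped or poorly followed FAB, although they are meant to explain partial adherence

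*Protocol article*

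**What the plan says.** All statements are from the protocol article.

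- **Method (Qualitative approach).** "In this feasibility study, we will use a convenience sampling technique for the qualitative work".
- **Number and balance (same section).** "we will aim to interview 10 patients (adjusted for setting, gender and age group representation"). Neither adherence nor discontinuation is a balancing factor.
- **Subject (same section).** The interviews "will help us understand the lived experience of people using FAB".
- **Purpose (same section).** Useful insight is expected from "triangulation between the RCT and the qualitative findings (for example, reasons for partial adherence").
- **Purpose (Data analysis, patient-oriented framework).** "Understand the lived experience of patients using FAB with emphasis on intervention acceptability, perceived enablers and barriers for adherence". The list ends with "factors relating to the initial uptake of the intervention".
- **Timing (Qualitative approach).** "This phase will work in parallel to the quantitative data collection so that emerging themes can be investigated in later interviews".

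Two other sections bear on the point. Outcome assessment records self-reported adherence to the intervention and the percentage of patients completing the study. Participant withdrawal lists, among the reasons for leaving, a sore finger when the patient does not want to use another, and a patient's own request, for instance because of inconvenient extra visits.

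**The concern.** To explain why patients follow FAB only partly, or stop, the interviews must include some patients who did so. The plan leaves this to chance. Convenience selection favours those who are easy to reach, which usually means those still attending and still using the treatment. A patient who has left because of sore fingers or inconvenience is likely to be harder to reach, and that patient's account bears most directly on acceptability. The three balancing factors do nothing to bring such patients in.

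The study exists to judge whether a definitive trial is feasible. If the interviews come mostly from continuing users, the account of acceptability may tilt in FAB's favour, and the barriers that a definitive trial should be designed around may be thinly described.

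**Working it through.** **Inputs from the article**

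- Recruitment target 60 (Sample size). The plan's figure is consistent with its inputs: 52 / (1 − 0.10) = 57.8, so 58, and 60 is 2 above that.
- 1:1 allocation (Randomisation procedures), so about 60 / 2 = 30 patients in Arm A.
- 10 patient interviews (Qualitative approach). No derivation is given, so there is nothing to reproduce.

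**Assumptions**

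- All 10 interviewees are in Arm A. This is inferred from the stated subject; the text says only 10 patients. If some came from Arm B, fewer Arm A patients would be interviewed and the probabilities below would rise.
- The number K of the 30 who stop or poorly follow FAB. The article gives no rate, so K = 3, 6 and 9 (10%, 20%, 30%) are shown.
- The selection weight w of a non-adherent patient relative to a continuing user. w = 1 is random selection; w = 0.5 and 0.25 are illustrations of convenience selection.

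**Random selection**

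P(none) = C(30 − K, 10) / C(30, 10)

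- K = 3: (20 × 19 × 18) / (30 × 29 × 28) = 6,840 / 24,360 = 0.281
- K = 6: (20 × 19 × 18 × 17 × 16 × 15) / (30 × 29 × 28 × 27 × 26 × 25) = 0.065
- K = 9: 0.012

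The expected number of non-adherent interviewees is 10K / 30, that is 1, 2 and 3.

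P(at most one) adds P(one) = K × C(30 − K, 9) / C(30, 10):

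- K = 3: 0.281 + 0.468 = 0.749
- K = 6: 0.065 + 0.261 = 0.326
- K = 9: 0.100

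**Selection with unequal weights**

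Drawing one patient at a time, the chance that none of the 10 is non-adherent is the product, over i = 0 to 9, of (30 − K − i) / (30 − K − i + wK). This is the Wallenius non-central hypergeometric distribution. With w = 1 it returns the random-selection values.

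| Non-adherent in Arm A (assumed) | P(none), w = 1 | P(none), w = 0.5 | P(none), w = 0.25 |
|---|---|---|---|
| 3 of 30 | 0.28 | 0.52 | 0.72 |
| 6 of 30 | 0.07 | 0.23 | 0.47 |
| 9 of 30 | 0.01 | 0.08 | 0.27 |

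At w = 0.5 the expected numbers of non-adherent interviewees fall to 0.58, 1.21 and 1.92.

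**Reading.** If non-adherence is about 10%, the interviews could easily contain no such patient, and would most likely contain at most one. At 20% or more, random selection would usually include at least one, and the problem then depends on how strongly convenience selection works against these patients. The article does not allow that strength to be estimated.

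**The case against.** The best defence is that this is a small nested study whose limits the authors admit. They confine convenience sampling to the feasibility stage, call the sample limited and aim for a larger one later. They expect to hear about partial adherence. They will also interview every clinician who administers the intervention, and they plan an analysis of treatment discontinuation. At 20% non-adherence, a random 10 would include at least one non-adherent patient about 93% of the time (1 − 0.065) and at least two about 67% of the time (1 − 0.326).

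Much of this stands. It shows a risk rather than a certainty, and it keeps the point modest. It does not remove the point. Clinicians give patients' reasons at second hand, and a discontinuation analysis gives rates and associations rather than reasons. Nor does a later, larger sample help the decision that this study is meant to inform.

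Three stronger readings are tempting, and the article does not support them.

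- **The interviews change the adherence being measured.** The statement about parallel working is made at study level, and its stated reason is to follow up themes in later interviews. It does not place a patient's interview before that patient's own adherence report. The within-patient schedule may be in the full protocol, which the article says is a supplementary file and which is not shown here.
- **Leaving out patients who declined the trial is an error.** Uptake is listed under the experience of patients using FAB, so the absence of decliners contradicts nothing. Outcome assessment already counts the percentage of eligible patients accepted for randomisation. Patients who fear needles or will not do repeat finger pricks are ineligible under the Exclusion criteria, so they are not eligible decliners.
- **Only patients for whom FAB worked will be interviewed, so partial adherence cannot be studied.** Nothing in the text restricts the sample in that way, and the probabilities above show that some non-adherent patients may well be included.

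**Conclusion.** The point holds as a limited mismatch between the stated sampling method and one of its stated purposes. The interviews are relied on for barriers to adherence and reasons for partial adherence, yet nothing in the selection makes it likely that patients who stopped or poorly followed FAB are heard.

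Under random selection, the chance of hearing none is 0.28 if 3 of 30 Arm A patients are non-adherent and 0.07 if 6 of 30 are. Convenience selection would probably raise these, to 0.52 and 0.23 if such patients are half as likely to be chosen. The figures rest on assumed non-adherence rates, an assumed selection weight, and all 10 interviewees being in Arm A. The trial's sample size, error rates and primary estimate are not affected. The change is worth making because it is cheap and uses information that the trial already collects.

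**What to change.** Keep 10 patient interviews and the spread over setting, gender and age group. Replace convenience selection with purposive selection on recorded adherence and discontinuation:

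1. First invite Arm A patients who stopped FAB or report low use, for example up to 4, or all of them if there are fewer. A fixed minimum of 4 would be impossible to meet if only 3 of 30 were non-adherent.
2. Fill the remaining places with continuing users.
3. Report how many patients of each kind were invited and how many were interviewed, so that a reader can see whose views the themes rest on.

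Recruitment was already open when the article was written, so the change would apply to interviews not yet held. The costs are slightly slower recruitment to interviews and some refusals among patients who withdrew, who should be approached only where their consent still allows it.

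Two additions are optional. Each interview could follow that patient's final adherence report. This fits the parallel design, because recruitment is spread over 12 months and themes can still be carried forward to later patients. A few interviews with eligible patients who declined would also be useful, but they need separate consent and an ethics amendment, and they would extend the plan rather than correct an error in it.

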### Economic evaluation

Good practice recommendations for cost-effectiveness analyses suggest concentrating on the measurement of large cost drivers, with less focus on resources that are not expected to differ between different treatments.^26^ Estimation of cost-effectiveness is therefore an iterative process and by including a health economic component in the feasibility it is possible to consider how the methods might be refined in any future definitive study. In order to estimate costs, informed by previous data collection instruments (Database of Instruments for Resource Use Measurement: http://www.dirum.org/) and National Institute for Health and Care Excellence guidance,^27^ a self-report resource use questionnaire will be devised. This will capture the use of NHS services and privately purchased over-the-counter treatments such as Optrex. For benefits, EQ-5D-5L^28^ will be used to measure QoL, enabling quality-adjusted life year scores to be calculated. The main purpose of the economic analysis is to inform the decision regarding how and what cost and effect data would be collected within a more definitive study. In order to inform this decision, we will estimate completion rates and seek to identify big cost drivers.

### Outcome assessment

The primary outcome measure is the proportion of eligible patients approached who consent to and comply with the trial protocol. This will be assessed by: number of eligible patients within the study population and recruitment time frame, percentage of eligible patients accepted for randomisation, patient compliance with trial protocol measured as per self-reported adherence to intervention and percentage of patients completing study. The secondary outcomes include reduction in corneal inflammation (assessed by the Oxford corneal staining guide), patient pain and symptoms scores (assessed by the OSDI Score) and improvement in objective signs of DED as indicated by visual acuity, Schirmer’s test, tear break-up time, lower and/or upper tear menisci height measurement. Other secondary end points include patients’ QoL (assessed using the EQ-5D-5L Questionnaire), cost to the NHS and patient (assessed via use of additional NHS services and privately purchased over-the-counter treatments related to DED) and safety measure of pressure within the eye (assessed by IOP Score).

### Data analysis

Detailed data validation will examine completeness, existence and accuracy of collected data to assess data quality and identify missing and conflicting data. Statistical analysis will be performed on an intention-to-treat basis ie, inclusion of patients randomly assigned, regardless of adherence, actual treatment received, and subsequent withdrawal of treatment and/or deviation from the protocol and per-protocol (ie, inclusion of those who completed the treatment as planned)^29^ and will be reported according to 2010 CONSORT guidelines.^30^ All statistical analyses will be completed using SPSS Statistics V.22.0.^31^ A value of p<0.05 will be accepted as statistically significant. Conforming to recommendations for feasibility studies, data analysis will be primarily descriptive, with means, SD and frequency counts calculated for all variables of interest.

Exploratory efficacy analysis will compare the primary outcome variables derived from the data collected at 8 weeks between the two arms using a marginal general linear model with robust standard errors, to allow for clustering by group. Secondary outcomes between the intervention and control groups will be compared at 4 weeks, 8 weeks and 12 weeks (4 weeks post-treatment). Safety outcome measures will include IOP rise and any reported infection. Secondary analyses of the primary outcome, controlling for baseline covariates, will be performed using proportional hazards regression models.^32^ Analysis of treatment discontinuation adjusted for clinical site, baseline status, and whether the patient is randomised to the FAB or control (conventional treatment only) group will be conducted. Any interaction between baseline status or regimen and treatment will also be assessed. Interactions between significant covariates and treatment effects will be assessed in the context of the proportional hazards models.

Interviews will be recorded, transcribed and analysed using the framework analysis. We will structure the analysis of collected data to fit two evaluation frameworks relevant to the successful implementation of FAB:Patient-oriented: Understand the lived experience of patients using FAB with emphasis on intervention acceptability, perceived enablers and barriers for adherence, perceived clarity of advice, and guidance and factors relating to the initial uptake of the intervention.Organisation-oriented: Whether and how the use of FAB affected workload and/or workflow; identify process change, adaptation challenges, skills gap; establish treatment fidelity and clinician acceptability.

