## Primary and secondary objectives

The primary objective is to determine the feasibility of a definitive randomised controlled trial (RCT) to evaluate effectiveness of the use of fresh autologous blood (FAB) compared with conventional treatment for patients with severe dry eye syndrome. The primary outcome is the proportion of eligible patients approached who consent to and comply with study procedure including treatment regimen and completion of required questionnaires. The secondary objectives, although not powered for within this feasibility include: to estimate the effectiveness of the trial intervention and further explore the acceptability of the study design, and to explore the feasibility of collecting resource use and QoL data to inform the design of the health economics component of a future definitive trial. The secondary outcome measures, although not powered for within this feasibility, include corneal inflammation (assessed by the Oxford Corneal Staining Guide), patient pain and symptoms scores (assessed by the Ocular Surface Disease Index (OSDI) Score) and objective signs of DED as indicated by visual acuity (assessed by Schirmer’s test, tear break-up time, lower and/or upper tear meniscus height measurement). Other secondary outcomes include patients’ QoL (assessed using the validated EQ-5D-5L Questionnaire), cost to the NHS and patient (assessed via use of NHS services and privately purchased over-the-counter treatment related to dry eye disease) and safety measure of pressure within the eye (assessed by the Intraocular Pressure (IOP) Score).

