#### Randomisation procedures

Randomisation will be carried out by the Anglia Ruskin Clinical Trials Unit (ARCTU) using the SEALED ENVELOPE randomisation service. SEALED ENVELOPE is a randomisation and online database service developed for clinical trial services. It is an internet-based system and will be set for this study by ARCTU in accordance with the protocol. Enrolled patients will undergo 1:1 block randomisation to Arm A or Arm B. The system stores the predetermined sequence of randomisation and this list is visible to neither the investigator nor the ARCTU staff. Once a patient has consented to take part in the trial, they will be randomly allocated either to Arm A to receive FAB and conventional therapy or to Arm B to receive conventional therapy only. The research nurse or fellow or designated staff will log on to a web browser application and enter the patient’s eligibility factors into the system. The treatment allocation will be sent to the research team who will make the necessary arrangements for the patient’s treatment plan.

The treating ophthalmologist in the clinic will prescribe and counsel all patients on the correct technique for conventional treatment. The unblinded research nurses will provide additional training to the patients on the method of delivering FAB, including the use of a training video. Patients will be advised by the research team to inform their ophthalmologist if they have been started on any new treatment during the trial period by other clinicians or themselves.

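### The 8-week exploratory efficacy model is assigned to the feasibility outcome, which has no value by arm and whose separable parts measure adherence and retention, not efficacy

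*Protocol article*

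**What the plan says.** Outcome assessment defines the primary outcome: "The primary outcome measure is the proportion of eligible patients approached who consent to and comply with the trial protocol". It is to be judged from the number of eligible patients and from "percentage of eligible patients accepted for randomisation, patient compliance with trial protocol measured as per self-reported adherence to intervention and percentage of patients completing study". Primary and secondary objectives gives the same definition and adds questionnaire completion to what compliance covers. All clinical measures (Oxford corneal staining, OSDI, Schirmer's test, tear break-up time and the rest) are secondary, and the wish "to estimate the effectiveness of the trial intervention" is a secondary, unpowered objective.

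Randomisation procedures fixes the order of events: "Once a patient has consented to take part in the trial, they will be randomly allocated either to Arm A".

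Data analysis then states: "Exploratory efficacy analysis will compare the primary outcome variables derived from the data collected at 8 weeks between the two arms". The method it names for this comparison is a marginal linear model with robust errors. The sentence after it reads "Secondary outcomes between the intervention and control groups will be compared at 4 weeks, 8 weeks and 12 weeks (4 weeks post-treatment", with no model named. The same section restricts intention-to-treat to randomised patients, defines per-protocol as "inclusion of those who completed the treatment as planned", and plans further analyses of the primary outcome by proportional hazards regression. It describes the analysis overall as mainly descriptive.

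**The concern.** A between-arm efficacy analysis needs a variable that every analysed patient has within an arm and that reflects clinical effect. The primary outcome fails on both counts. Its denominator is set before anyone has an arm, and it counts who agrees and complies, not how the eyes fare.

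Two things are at stake. A difference in adherence or drop-out could be published under the word efficacy, with a p-value, since the section sets a 0.05 threshold without exempting the feasibility outcome. And the analyst must guess which variable enters the only model specified for efficacy, possibly after seeing the data. Because the trial is meant to inform a definitive study, readers may give that result more weight than it can bear.

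**Working it through.** **1. Inputs.** From Sample size: 52 evaluable patients (26 per arm), 10% attrition, 60 to be recruited. From Outcome assessment and Randomisation procedures: the outcome definition and the order of consent and allocation. The article states no expected consent or compliance rate, so those below are assumptions.

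**2. The plan's own figure.** 52 / (1 − 0.10) = 57.8, rounded up to 58. The stated 60 agrees with this after further rounding. I take 60 as the number randomised, 30 per arm.

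**3. Does the primary proportion have a value by arm?** Let M be the number approached, R the number randomised and C the number who consent and comply. The outcome is C / M. Arm values would need M to divide into two arms, but M − R patients were never allocated. With R = 60, consent rate c, M = 60 / c and an assumed C = 48:

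| Assumed c | M | No arm (M − 60) | C / M |
|---|---|---|---|
| 50% | 120 | 60 | 0.40 |
| 70% | 86 | 26 | 0.56 |
| 94% | 64 | 4 | 0.75 |
| 100% | 60 | 0 | 0.80 |

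Only if everyone approached consents does the proportion divide by arm. The 94% row is close to the exploratory study described under Rationale and risks/benefits: 16 took part and one eligible patient declined, so 16 / 17 = 0.94.

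**4. Which components can be split by arm?**

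| Component | Before or after allocation | Comparable by arm? | What it measures |
|---|---|---|---|
| Number eligible | Before | No | Size of the pool |
| Share accepted for randomisation | Before | No | Consent |
| Self-reported adherence | After | Yes | Adherence |
| Study completion | After | Yes | Retention |

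None measures clinical effect. Adherence also differs in meaning between arms: Arm A has finger-prick blood plus conventional treatment, Arm B conventional treatment only.

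**5. What the model could report.** Suppose 22 of 30 comply in Arm A and 26 of 30 in Arm B (assumed; total 48). Then 22/30 − 26/30 = 0.733 − 0.867 = −0.133. Under the current wording this 13-point adherence gap would be the exploratory efficacy result, although no staining grade or symptom score entered it.

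**6. Per-protocol set.** Membership requires having completed treatment as planned. Within that set, treatment adherence is therefore fixed by selection in both arms, and comparing it is circular. Questionnaire completion and attendance to week 12 are not fixed in this way, because they are not part of the membership rule.

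**7. Clinical outcomes.** They do have a between-arm comparison at week 8, through the secondary-outcome sentence. What is missing is any link between a clinical outcome and the model named for efficacy.

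**The case against.** The best reply is that the sentence speaks of variables in the plural, taken from 8-week data. Patients who decline have no such data, so it may mean only adherence and completion among randomised patients. Both can be compared by arm, and doing so is a fair feasibility question. That answers the denominator difficulty on this reading. It does not answer the label: adherence and completion are still not efficacy.

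A reader might also infer four stronger things that the article does not support:

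- **That no between-arm clinical estimate is planned at 8 weeks.** The next sentence plans one for all secondary outcomes, and means and SDs are promised for all variables of interest. The method for them may lie in a plan not shown.
- **That the per-protocol difference in the primary outcome must be zero.** Only the treatment-adherence part is fixed. A patient may finish treatment yet miss a questionnaire or the last visit.
- **That a linear model is wrong for a yes/no outcome.** With robust standard errors it can give a usable risk difference.
- **That half the denominator would have no arm.** That needs 50% consent, which is an assumption. At the exploratory study's rate it would be about 4 of 64.

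It is also true that the analysis is labelled exploratory, that effectiveness is unpowered, and that the overall feasibility proportion can be calculated regardless. This limits the severity but does not remove the inconsistency.

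**Conclusion.** The point holds as a mismatch between outcome and analysis. The named 8-week efficacy model is attached to feasibility variables. The overall proportion has no arm-specific value unless every approached patient consents, and the parts that do have one measure adherence and retention. No clinical outcome is assigned to that model, although clinical outcomes are compared elsewhere as secondary outcomes. In the per-protocol set the treatment-adherence part is also circular.

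This conclusion rests on the wording and the order of consent and allocation, not on any assumed rate. The number without an arm depends on consent: 60, 26, 4 or 0 at assumed rates of 50%, 70%, 94% or 100%. It should be fixed, but it does not threaten the trial, because the analysis is exploratory and mainly descriptive.

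**What to change.** Amend the Data analysis section as follows.

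1. Report consent among approached patients, and the consent-and-comply proportion, each as one overall estimate with a 95% confidence interval.
2. Report adherence, questionnaire completion and retention among randomised patients, overall and descriptively by arm. Do not label these efficacy, and do not report treatment adherence in the per-protocol set.
3. Assign the 8-week exploratory efficacy model to named clinical outcomes already collected, for example Oxford staining and OSDI, in all randomised patients.
4. Align the proportional hazards sentence with this, by naming the variable it analyses in place of the primary outcome.

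The cost is a change of wording, best made before anyone sees outcome data by arm. It needs no new data, visits or patients.

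### The models the plan names for efficacy are attached to the feasibility outcome, not to the clinical outcomes

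*Protocol article*

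**What the plan says.** The Outcome assessment section of the protocol article gives a single primary outcome: "The primary outcome measure is the proportion of eligible patients approached who consent to and comply with the trial protocol". It is assessed by four components. The first two are the "number of eligible patients within the study population and recruitment time frame, percentage of eligible patients accepted for randomisation". The last two are "patient compliance with trial protocol measured as per self-reported adherence to intervention and percentage of patients completing study". The abstract and the objectives section give the same primary outcome.

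The clinical measures (Oxford staining grade, OSDI, visual acuity, Schirmer's test, tear break-up time and tear meniscus height) are all listed as secondary. One secondary objective is "to estimate the effectiveness of the trial intervention and further explore the acceptability of the study design".

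The Data analysis section then says: "Exploratory efficacy analysis will compare the primary outcome variables derived from the data collected at 8 weeks between the two arms", and names the model: "using a marginal general linear model with robust standard errors, to allow for clustering by group". The next sentence compares the secondary outcomes by arm at 4, 8 and 12 weeks and names no model. Covariate-adjusted proportional hazards models follow, again on the primary outcome, and treatment effects and interactions are to be examined within them. A separate sentence plans an adjusted analysis of treatment discontinuation.

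On timing, the Randomisation procedures section states: "Once a patient has consented to take part in the trial, they will be randomly allocated either to Arm A" or to Arm B.

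**The concern.** An efficacy analysis should compare a measure of benefit between the arms. The outcome assigned to it here counts people who agree to join, comply and finish. Part of it is settled before any patient has an arm, and the rest describes how acceptable the treatment and the study are.

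Two things are at stake. First, the effectiveness objective has no named model behind it, while the models that are named answer another question. Secondly, a result published under the label of efficacy could be a difference in compliance or completion. FAB asks for finger pricks four times a day, so compliance could plausibly differ by arm whether or not symptoms improve. The section also sets a 5% significance threshold, so such a difference could be reported as a significant or non-significant efficacy finding.

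**Working it through.** The point is mainly one of consistency between sections. The arithmetic only shows scale.

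**1. The plan's own figure.** The Sample size section wants 52 patients (26 per arm) and allows for 10% attrition: 52 / (1 − 0.10) = 57.8, rounded up to 58, or 26 / 0.9 = 28.9, rounded up to 29 per arm. The stated target of 60 is two above this. The sample size is not in dispute; 60 (30 per arm) and 26 per arm are used below.

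**2. The four components against the time of allocation.**

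| Component (Outcome assessment) | Relative to allocation | Contrast between arms? | Clinical benefit? |
|---|---|---|---|
| Number eligible | Before | No | No |
| Percentage accepted for randomisation | Before | No | No |
| Self-reported compliance | After | Yes, though its meaning in Arm B needs stating | No |
| Percentage completing | After | Yes | No |

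Two of four have no contrast between arms, and none of the four measures clinical benefit.

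**3. Why the primary proportion cannot be formed by arm.** Its denominator includes patients who decline, and they are never allocated. Among randomised patients the consent part is 100% in both arms. To randomise 60 at a consent rate c, about 60 / c must be approached. The article gives no expected rate, so c is an assumption:

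- c = 50%: 60 / 0.5 = 120 approached, 60 without an arm
- c = 70%: 60 / 0.7 = 85.7, so 86 approached, 26 without an arm
- c = 90%: 60 / 0.9 = 66.7, so 67 approached, 7 without an arm

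At any consent rate below 100%, some of the denominator belongs to neither arm.

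**4. What remains comparable.** Compliance and completion remain. With 30 per arm, the 95% half-width for a difference in proportions is 1.96 × √[p₁(1 − p₁)/30 + p₂(1 − p₂)/30]. Over assumed rates:

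- 90% v 90%: 1.96 × √0.006 = 0.15
- 70% v 90%: 1.96 × √0.010 = 0.20
- 50% v 90%: 1.96 × √0.01133 = 0.21

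That is useful feasibility information, but it says nothing about symptoms or staining.

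**5. What the same trial gives on a clinical outcome.** With 26 per arm and no baseline adjustment, the 95% half-width for a mean difference is 1.96 × √(2/26) = 0.54 SD. This does not measure the error. It shows that a retargeted model would give an imprecise but interpretable estimate from data already being collected.

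**6. The proportional hazards models.** They sit on the same primary outcome, so they repeat the mismatch. A proportion who consent and comply has no event time as defined. Treatment discontinuation, which the same section already plans to analyse, does.

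**The case against.** The strongest reply is that this is loose wording in an exploratory paragraph. The sentence right after the disputed one compares the clinical outcomes by arm at three visits. Means and SDs are promised for every variable of interest, so the SD wanted for the full-scale trial does not depend on the disputed model. A condensed article may leave the model for secondary outcomes to the full protocol or analysis plan. The disputed sentence is also limited to 8-week data, so it need not be read as asking for a contrast in consent. Compliance can be defined in Arm B too, since those patients have a conventional regimen and questionnaires to complete. No decision in the article hangs on the p-value, and effectiveness is stated to be unpowered.

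Most of this stands, and it rules out three stronger readings that a reader might infer:

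- *The plan cannot estimate FAB's effect.* It can, through the secondary comparisons.
- *The primary outcome is largely fixed before randomisation, so that only completion is comparable.* Two components of four are fixed before allocation; compliance and completion can both be compared by arm.
- *The marginal model is the only one named for treatment effects.* Proportional hazards models are named as well, although on the same outcome.

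The reply does not remove the mismatch. The missing model for the secondary outcomes may fairly be left to another document and is not the complaint. The complaint is that the article assigns its efficacy label and its models to an outcome that it defines elsewhere as feasibility. An analysis plan that followed this text would inherit the error, and one that corrected it would contradict the article. Limiting the sentence to 8-week data leaves compliance and completion, which are still not efficacy.

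**Conclusion.** The concern holds in a limited form. The exploratory efficacy model and the proportional hazards models are placed on an outcome that measures feasibility. Two of its four components have no contrast between arms, and the other two measure acceptability and retention. The clinical effect can still be estimated from the planned secondary comparisons, but not by the models the plan names for efficacy.

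Severity is moderate. A reader might infer that the trial's conclusions are at risk, but the documents do not support that: the analysis is exploratory, unpowered and mainly descriptive, and the primary feasibility question is unaffected. The verdict rests on the article's own definitions and on allocation following consent. It does not depend on the assumed consent or compliance rates, which only show scale.

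**What to change.** In the Data analysis section:

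1. Make clinical secondary outcomes at 8 weeks the targets of the exploratory efficacy model, and name them before the data are seen. OSDI and Oxford grade are examples; the article does not rank its secondary outcomes, so the choice is the investigators'. Report between-arm estimates with 95% confidence intervals, on a scale suited to each outcome (the Oxford grade is ordinal).
2. Take the primary outcome out of the efficacy analysis and report it descriptively: consent over all eligible patients approached, then adherence and completion by arm, with a statement of what adherence means in Arm B.
3. Restrict the proportional hazards model to a time-to-event outcome, such as treatment discontinuation. Changing only the efficacy sentence would leave the same mismatch here.

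The cost is a few sentences and the need to commit in advance to the lead clinical outcome or outcomes. No new data, visits or patients are required, and the sample size does not change.
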